### Ethics Approval and Consent to Participate

The PROUDEST was approved by the Research Ethics Committee of the University of Brasilia School of Medicine (Certificado de Apresentação de Apreciação Ética 32359620.0.0000.5558) [45]. It was also registered in the Brazilian Register of Clinical Trials [46]. All pregnant women participating in the PROUDEST are required to sign an informed consent form to join the PREGNANT branch. Likewise, the participation of the children in the BORN branch will require signed, informed consent from their mothers. The 6-month reports on the study’s status and its partial results will be made available to the institutional Research Ethics Committee and may be publicly consulted upon request.

### Availability of Data and Materials

At the time of the publication of this protocol, study enrollment and data collection have already started, but we have not completed the participant recruitment and data analysis phases. Therefore, data sharing is not yet feasible, as no data sets have been generated or analyzed at this stage of the study. As partial data become available, they will be displayed in the Brazilian Register of Clinical Trials [46].

## Results

The PROUDEST is in the data collection phase. Study recruitment started in July 2020. As of January 2021, a total of 260 pregnant women who were infected with SARS-CoV-2 during pregnancy and 180 newborns from hospitals in the Federal District in Brazil have been included in the study. Data analysis is scheduled to start after all data are collected.

## Discussion

### Study Implications

The PROUDEST offers comprehensive insight (from both the obstetric and pediatric perspectives) into the effects of SARS-CoV-2 infection on the global health of pregnant women and their offspring. Specifically, the study will fill the deep gap in knowledge about the consequences of SARS-CoV-2 infection during early gestation (ie, the period when the critical stages of embryogenesis take place), as women in all stages of pregnancy will be followed. The virus-induced inflammatory and immunological phenomena that occur in SARS-CoV-2–exposed mothers during this early period of life may have a particular impact on placental and fetal physiology or may even be associated with epigenetic signals. Therefore, these phenomena could conceivably affect the long-term outcomes of a child’s growth, development, and metabolism.

A better understanding of these potential long-term consequences requires lengthy, prospective observational studies, such as the PROUDEST. This study will not only address the clinical outcomes associated with in-pregnancy exposure to COVID-19 but also evaluate a host of soluble tissue biomarkers (as described in this protocol) with the aim of comprehensively understanding the mechanisms underlying related clinical phenomena.

Our data will add to the overall clinical and basic knowledge base for COVID-19, and our ultimate goal is to provide grounds for better managing SARS-CoV-2–exposed pregnant women and their children through direct means or by setting the stage for additional studies. In fact, the PROUDEST opens up a broad spectrum of possibilities for further, multidisciplinary research on the effects of SARS-CoV-2 infection on maternal, fetal, and pediatric health. Furthermore, our results might prove to be relevant from a social perspective, as they may provide data that support the tailored development and implementation of health policies that are specifically oriented to this particular demographic group.

The study does have several limitations. Its observational nature limits inferences for causal associations to some extent. However, the cohort study design is the closest observational equivalent to a clinical trial in terms of analytical power, and the objective of the PROUDEST does not ethically allow for interventional experiments because such experiments would imply that pregnant woman will be randomized based on SARS-CoV-2 infection. Moreover, the purpose of the study is to characterize the clinical and pathophysiological phenomena associated with SARS-CoV-2 infection during pregnancy and infancy, not to test the efficacy of any intervention. Thus, we believe that a cohort study is the best possible study design for addressing our objectives. The lack of random allocation for comparison groups will be partially compensated by statistically adjusting for the observed imbalances. Vaccination for SARS-CoV-2 will not be an exclusion criterion because due to the vaccine’s limited accessibility and availability, there are no feasible methods for estimating the proportion of pregnant women that will receive the vaccine. However, the effects of SARS-CoV-2 vaccination can be adjusted and analyzed in small control groups that have either received or not received the vaccine.

The protracted follow-up in the BORN substudy is expected to result in the dropout of several participants. We set a sample size for the study after taking into consideration a 20% loss to follow-up rate. This might ensure that a sizable number of children are available for the final assessment when they reach age of 5 years. However, we cannot avoid survival bias in the long-term data. Nevertheless, given that the continuity of multidisciplinary assistance will be guaranteed for all children in the BORN branch throughout the study period regardless of their withdrawal from the analysis or (temporary) losses to follow-up, we expect that children experiencing health problems associated with in-pregnancy COVID-19 exposure will be less likely to drop out than those who are in perfect health. Therefore, we do expect to have a sufficient number of children in the long run for identifying developmental abnormalities (should they exist), even after some amount of dropout.

Several routine pediatric consultations will be emphasized in the study, such as checking the kind of alimentation that a child is receiving (human milk or formula milk) and promoting the practice of breastfeeding.

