### Sample Size Calculation

No precise data are available on the prevalence of SARS-CoV-2 infection among pregnant women in Brazil, but international reports have estimated that up to 15.3% of all pregnancies have been exposed to the virus [38]. Recent data have indicated a birth rate of 44,195 newborns per year in the Federal District [39]. Thus, after considering an “infinite” population (>20,000 pregnant women), assuming a 15% prevalence of SARS-CoV-2–exposed pregnancies, and accounting for a confidence level of 95% and a margin of error of 5%, the minimum sample size for a random sample of SARS-CoV-2–exposed women would be 195. This calculation expectedly yielded a similar number for a random sample of SARS-CoV-2–exposed children. If we set the expected dropout rate for the BORN substudy to 20%, the required number of SARS-CoV-2–exposed mothers (those giving birth to the BORN participants) would increase to 234.

Our sampling approach however is not truly random; it is based on convenience, as eligible subjects will present to the recruitment centers. The aforementioned calculations only serve as a reference for avoiding the overestimation of the inclusion of participants. Given the limited amount of available knowledge regarding the effects of SARS-CoV-2 infection on pregnancy and child development, which resulted in the eminently exploratory character of our study, we adopted an “as much as feasible, but no more than reasonable” approach for defining the sample size.

We set an a priori number of 300 SARS-CoV-2–exposed women for the PREGNANT phase. This will result in the inclusion of the expected 300 SARS-CoV-2–exposed children in the BORN phase. The subject allocation rate between the exposed and control groups was 1:1. This indicated the need for an additional 300 mothers and 300 children to constitute the nonexposed control groups. Hence, the overall sample size of the PROUDEST was set to 1200 participants (600 mother-child dyads consisting of 300 SARS-CoV-2–exposed mother-child dyads and 300 control dyads).

To promote participant retention and completed follow-ups at pregnancy and pediatric outpatient clinics, we will actively search for patients via phone and email.

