All newborns will undergo neonatal screening tests in accordance with the recommendations of the Ministry of Health of Brazil. Five drops of blood will be collected on filter paper for the national neonatal screening program. This blood sample will be collected after 48 hours of life and will be used to screen for the following diseases: phenylketonuria, congenital hypothyroidism, biotinidase deficiency, cystic fibrosis, and congenital adrenal hyperplasia. After 24 hours of life and before discharge, a pulse oximetry test will be performed. Oxygen saturation in the right upper limb and one of the lower limbs will be measured. The pulse oximetry test will be considered normal if oxygen saturation is ≥95% and the difference between the limbs is not ≥3%. Hearing screening will be performed between 36 and 48 hours of life by analyzing otoacoustic emissions.

After hospital discharge, all neonates will be followed up at the Pediatric Outpatient Clinic of the University Hospital of Brasilia. Child growth and neurodevelopment will be assessed at all visits. The first visit will be scheduled to occur on day 15 postpartum. Afterward, visits will be conducted monthly during the first 6 months of life. Thereafter, visits will be scheduled every 3 months until the children reach 12 months of age and every 6 months until the children reach 5 years of age. Nonscheduled visits may occur due to urgent clinical needs. The outpatient clinic staff (a multidisciplinary team) will be composed of pediatricians, psychologists, occupational therapists, speech therapists, physiotherapists, and nurses. The psychological effects of SARS-CoV-2 infection on mothers will be assessed with the Edinburgh Postnatal Depression Scale [42]. This assessment will occur more than once until their children reach 6 months of age. Breastfeeding and weaning patterns, dietary habits, nutritional status, and vaccinal status will be assessed throughout the study.

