### Statistical Analysis

All data will be stored in REDCap (Research Electronic Data Capture; Vanderbilt University), which is a tool for building and managing web-based surveys and databases. All variables will be summarized via standard descriptive techniques according to their type and distribution. For the bivariate analysis, differences in categorical variables between the exposed and unexposed groups will be verified with the Chi-square test or Fisher exact test, whereas differences in continuous variables between the groups will be assessed with the Student *t* test or the Mann-Whitney U test.

For dichotomous outcomes, binomial regression models, which will be adjusted based on the unbalanced and relevant background features of the comparison groups, will be used to estimate the relative risks between the exposed and nonexposed groups. Partial correlation and general linear models will be used to assess the associations between continuous outcome variables and covariates; adjustments for imbalances will be made as appropriate. A *P* value of <.05 will be considered significant. The control group will be composed of nonexposed mother-child dyads that meet the inclusion criteria. However, those with positive serology tests (IgG and IgM tests conducted at 14-21 days postpartum) will not be included in the control group. The groups will not be matched or paired based on age or other variables. However, any differences between the groups will be adjusted later via statistical means.

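### The protocol article offers the expected dropout of healthy children as reassurance, but that pattern overstates the risk of abnormality and, if it differs by exposure group, distorts the relative risk

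*Protocol article*

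**What the plan says.** All places are in the protocol article.

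- **Discussion, Study Implications (limitations).** The authors concede: "However, we cannot avoid survival bias in the long-term data". They go on to argue that, because care continues for every child in BORN, "children experiencing health problems associated with in-pregnancy COVID-19 exposure will be less likely to drop out than those who are in perfect health". From this they conclude that "we do expect to have a sufficient number of children in the long run for identifying developmental abnormalities".
- **Sample Size Calculation.** The loss allowed for in BORN is 20%. The target is 300 exposed and 300 control children.
- **Procedures.** "Child growth and neurodevelopment will be assessed at all visits", and intelligence is tested every 6 months from the age of 2.5 years. Follow-up runs to 5 years.
- **Statistical Analysis.** Categorical variables are compared by chi-square or Fisher exact test, and continuous variables by Student t or Mann-Whitney test. Relative risks come from binomial regression, and continuous outcomes are modelled by partial correlation and general linear models. The stated adjustment is for imbalances in background features between the groups.

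**The concern.** The Discussion predicts loss to follow-up that depends on the outcome: well children leave and children with problems stay. It treats this as a strength. A sufficient number of affected children helps detection in the sense of having cases to describe. It does not give an unbiased risk, mean score or relative risk, because those also depend on the well children who have left.

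The expected retention is tied to problems linked with in-pregnancy exposure, so it may act more strongly in the exposed group. In that case the group comparison is distorted as well as the prevalence. Adjusting for background differences does not remove loss driven by a child's later health.

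The stake is aim 9 in the Objective section, the effect of exposure on child development up to 5 years. The authors intend their findings to inform care and policy.

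**Working it through.** **1. The plan's own figures.** The inputs are a prevalence of 15%, 95% confidence and a 5-point margin.

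- n = 1.96² × 0.15 × 0.85 / 0.05² = 195.9. With a finite-population correction for 44,195 births it is 195.05. The stated 195 is reproduced.
- The stated 234 is 195 × 1.20. Dividing by the retained fraction gives 195 / 0.80 = 244. This is a separate matter, and the planned 300 covers it.
- Children remaining per group after 20% loss: 300 × 0.80 = 240.

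**2. Prevalence among those who remain.** Let p be the true prevalence of abnormality, D the overall loss and d the loss among abnormal children. Then

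observed prevalence = p(1 − d) / (1 − D).

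D = 20% is the plan's figure. The document gives neither p nor d, so both are assumed. With p = 10%, 30 of 300 children are abnormal:

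| Loss among abnormal children, d | Loss among well children | Observed prevalence | Ratio to truth |
|---|---|---|---|
| 20% (unrelated to health) | 20.0% | 24/240 = 10.0% | 1.00 |
| 10% | 21.1% | 27/240 = 11.25% | 1.125 |
| 5% | 21.7% | 28.5/240 = 11.9% | 1.19 |
| 0% | 22.2% | 30/240 = 12.5% | 1.25 |

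The ratio (1 − d)/(1 − D) does not depend on p. Its ceiling is 1/(1 − D): 1.25 at 20% loss, 1.43 at 30% and 1.67 at 40%.

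**3. Effect on the relative risk when exposure has no effect.**

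- *Pattern in the exposed group only, with controls losing 20% regardless of health:* the apparent relative risk equals the ratio above, so 1.125 (d = 10%) to 1.25 (d = 0).
- *Same pattern in both groups:* the apparent relative risk is 1.00, and prevalence is overstated equally in both.

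**4. False-positive rate.** This was simulated with 300 enrolled per group, no true effect, a two-sided pooled test of two proportions at 5%, and 40,000 repetitions.

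| True prevalence (assumed) | Exposed group only, d = 10% | Exposed group only, d = 0 | Both groups, d = 0 |
|---|---|---|---|
| 5% | 6.1% | 9.2% | 4.9% |
| 10% | 7.2% | 13.7% | 5.0% |
| 15% | 8.8% | 19.5% | 4.9% |
| 20% | 10.2% | 26.0% | 4.9% |

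**5. Equal retention with a true effect.** Take assumed true risks of 20% and 10%, with all abnormal and 78% of well children retained in both groups. The observed risks are 0.20/(0.20 + 0.80 × 0.78) = 24.3% and 0.10/(0.10 + 0.90 × 0.78) = 12.5%. The relative risk is 1.95 instead of 2.00, a small bias towards 1.

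**The case against.** The strongest reply has four parts.

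- **Survival bias is already listed as a limitation, and families are to be actively sought by phone and email.** This is true and should be credited. But the concession gives no direction, and the next sentence sets it aside.
- **The conclusion drawn is about having enough children, not about an unbiased relative risk.** That is a fair reading of the words. However, a study whose stated analysis estimates relative risks cannot rest its reassurance on the number of cases alone.
- **The reason given for retention, continued care, applies to all BORN children, so nothing shows that controls are lost regardless of health.** This stands as a condition on the relative-risk result. With no true effect, a false one needs something more, such as families attributing problems to the exposure. Equal retention cannot be presumed either: the sentence ties retention to exposure-associated problems. Study Design also removes later-infected controls from analysis and states no matching rule for exposed children.
- **The size is modest.** Even in the extreme case, 30/240 against 24/240, the relative risk of 1.25 has an approximate 95% interval of 0.75 to 2.07, so the bias is under one standard error. This is correct, but at 10% prevalence the same case raises the false-positive rate from 5% to about 14%.

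A reader might also infer that the plan tests single time points and discards earlier visits. The article does not say so. It names families of methods, and a fuller analysis plan may add longitudinal or missing-data methods. The point rests on the reasoning in the Discussion, not on a missing section.

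**Conclusion.** The concern holds in a limited form. The article predicts health-dependent dropout and uses it as reassurance, when it is a source of bias.

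- **Prevalence:** overstated by up to 1.25 times at 20% loss (a true 10% appears as 11.3% to 12.5%). This follows from the predicted pattern. Only the prevalence and the split of dropout by health are assumed.
- **Relative risk:** a true 1.00 appears as about 1.13 to at most 1.25, only if the pattern acts in the exposed group and not in controls. The upper figure also needs no abnormal exposed child to be lost.

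A reader might conclude that the relative risk is bound to be pushed away from 1. The document does not support that: with equal retention the null value is unchanged, and a true effect is slightly diluted. Nor does the document make the 5-year comparison the main result of BORN. It describes outcomes from birth up to 5 years, names no primary age and calls the study exploratory.

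**What to change.** 1. **Discussion.** State the expected dropout pattern as a bias, with its direction (prevalence overstated, and the relative risk affected if retention differs by group). Remove it as grounds for reassurance.
2. **Serial growth and developmental scores.** Analyse them with a linear mixed model on all visits, with group, age, group-by-age, baseline covariates and child random effects. A child's earlier results then inform the later missing ones.
3. **Binary outcomes at a given age.** Add an analysis with inverse-probability-of-censoring weights, built from group, baseline factors and the last observed growth and developmental results. Report it alongside the unweighted one.

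No new data are needed, and the Results section says that analysis starts only after collection ends. The cost is plan wording, more analysis work and somewhat wider intervals. Both methods correct the bias only as far as dropout is explained by observed data. Loss driven by health changes that were never recorded would remain.

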### Conclusions

The PROUDEST is a long-term, prospective cohort study designed to provide a comprehensive analysis of the effects of in-pregnancy exposure to COVID-19 on women and their offspring from a clinical and pathophysiological standpoint. Our results might contribute to the improvement of the management of SARS-CoV-2–exposed mother-child dyads—through direct means or by setting the stage for future related studies—by providing knowledge on the clinical-pathophysiological phenomena associated with COVID-19 exposure among this particular population.

## Abbreviations

CCL: CC motif chemokine ligand
CNS: central nervous system
CSF: cerebrospinal fluid
CXCL: CXC motif chemokine ligand
IgG: immunoglobulin G
IgM: immunoglobulin M
IL: interleukin
MERS-CoV: Middle East respiratory syndrome coronavirus
PROUDEST: Pregnancy Outcomes and Child Development Effects of SARS-CoV-2 Infection Study
REDCap: Research Electronic Data Capture
RT-PCR: reverse transcriptase–polymerase chain reaction
SARS-CoV: severe acute respiratory syndrome coronavirus
